#### Secondary outcomes

2.5.2

The secondary outcomes include mean changes in menstrual period, levels of estradiol, LH, FSH, and total testosterone, LH/FSH ratio, antral follicle count in the ovary, ovarian volume, BMI, waist-hip ratio (WHR), acne severity, and 36-item short-form health survey (SF-36) scores from baseline to 16 weeks and 32 weeks after the start of the trial.

The menstrual period is defined as the number of days from the first day of the menstrual cycle to the first day of the next menstrual cycle. It is assessed in order to evaluate the restored regular menstrual period.^[16]^ The levels of serum estradiol, serum LH, serum FSH, and total testosterone, and LH/FSH ratio will be estimated to evaluate the participant's sex hormone changes after interventions.^[^2^,^^20^^]^ The morphologic features of polycystic ovaries will be assessed by antral follicle count and ovarian volume via ultrasound imaging. A transvaginal transducer with frequencies of ≥8 MHz detects follicles with diameters in the range of 2 to 9 mm in the ovary and can be used to estimate ovarian volume.^[21]^ Follicular excess and ovarian enlargement are considered accurate markers of polycystic ovarian morphology.^[2]^ The participants’ obesity level will be assessed using BMI and WHR. BMI is defined as the body weight (kg) divided by the square of the height (m^2^). WHR is calculated using the circumference of the waist and hip.^[^22^,^^23^^]^ The acne severity will be assessed using the Pillsbury acne grading system, with grades ranging from 0 to 4. A high-scoring grade indicates more severe acne, that is, grade 0 is considered normal and grade 4 is considered to be severe.^[24]^ We will also assess the quality of life as reflected by an SF-36 score for the participants. The SF-36 questionnaire has been proved to be valid and reliable in each country. It will be used to assess the health-related quality of life of women with PCOS.^[^25^,^^26^^]^ The SF-36 questionnaire is a 36-item, patient-reported survey of patient health consisting of eight subscales, with a total score ranging from 0 to 100. The higher the score, the lesser the disability, that is, a score of 0 is equivalent to maximum disability and that of 100 is equivalent to no disability.^[27]^

### Safety and adverse events

2.6

Complete blood count and liver and renal functions will be examined to determine the safety of the acupuncture technique at screening and at 16 and 32 weeks after the start of the trial. Laboratory data will be recorded in a case report form (CRF) by the investigators. All expected or unexpected adverse events in both groups will be assessed at every visit. The participants will be asked to record any adverse events in their CRF throughout the study. All adverse events will be described in the CRF. Participants who suffer from the adverse effects of acupuncture will be treated or compensated according to insurance regulations.

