### Interventions

2.4

This study protocol follows the Standards for Reporting Interventions in Clinical Trials of Acupuncture (STRICTA) recommendations. The participants will be randomly assigned to an acupuncture group or a control (usual care) group in a ratio of 1:1. They will receive interventions and undergo assessments at scheduled visits. Acupuncture will be performed according to a fixed protocol by Korean and Chinese medicine practitioners who have official licenses and at least 2 years of clinical experience. Patients in the acupuncture group will undergo acupuncture therapy 10 times in 4 weeks for 16 weeks, resulting in a total of 40 sessions. Disposable, sterilized, stainless steel single-use needles (0.25 × 40 mm and 0.30 × 50 mm; Dongbang Medical Co. Ltd, Republic of Korea and Qingdao Dongfang Medical Equipment Co., Ltd., China, respectively) will be inserted at a depth of 10 to 50 mm at acupuncture points located in the head, abdomen, lower back, and upper and lower limbs. In total, 18 needles will be used for each participant in a set. The acupoints include GV20 (Baihui), CV4 (Guanyuan), and bilateral BL32 (Ciliao), ST25 (Tianshu), ST29 (Guilai), EX-CA1 (Zigong), LI4 (Hegu), LR3 (Taichong), SP6 (Sanyinjiao), and SP9 (Yinlingquan) and are based on the traditional medicine theory and consensus among experts about acupuncture and PCOS.^[16]^ The location of the acupuncture points is based on the “Nomenclature and location of acupuncture points”^[17]^ and the consensus of experts. All needles will be stimulated manually by rotation until a needle sensation (“de-qi”) is evoked. The patient will be in the prone position first, and the needle will be inserted at the BL32 acupoint at an angle of 30 to 45° in an inferomedial direction and a depth of 30 to 50 mm. Once the patient feels the “de-qi,” the needle will be immediately removed. The patient will then be shifted to the supine position, and GV20, CV4, ST25, ST29, EX-CA1, LI4, LR3, SP6, and SP9 will be needled to a depth of 10 to 40 mm. After the “de-qi” sensation is felt by the patient, the needles will be kept in place for 20 minutes to maintain stimulation. Furthermore, patients will be advised to manage themselves with usual care, similar to that used by the control group.^[18]^

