The participants in the control (usual care) group will be managed with the usual care regimen only. They will receive health advice and lifestyle management brochures regarding diet along with regular meals, sufficient sleep, and appropriate exercise once a month for 16 weeks.

The participants are not permitted concomitant medication like OCPs or ovulation induction that may affect menstrual cycles. And, acupuncture, moxibustion, cupping, and other traditional Chinese/Korean medicine treatments are neither allowed if they are judged to affect the outcome measures.

Adherence to acupuncture will be checked every 4 weeks during the treatment period, and participants who have an adherence rate of less than 70% will be dropped out.

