### Participant timeline

2.7

The schedule for enrollment, interventions, assessment, and visits of the participants are shown in Table 1.

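### Adverse-event enquiry tied to every visit risks unequal ascertainment: about 40 acupuncture sessions against about monthly control contacts

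*Protocol article*

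**What the plan says.** Section 2.6 (Safety and adverse events) of the protocol article sets the enquiry rule: "All expected or unexpected adverse events in both groups will be assessed at every visit". The next sentence adds a second route: "The participants will be asked to record any adverse events in their CRF throughout the study". Blood count and liver and renal function are tested at screening and at weeks 16 and 32, with no difference between arms stated.

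Section 2.4 (Interventions) fixes the contacts. The acupuncture arm receives "acupuncture therapy 10 times in 4 weeks for 16 weeks, resulting in a total of 40 sessions". Controls receive advice and brochures "once a month for 16 weeks"; the form of that contact is not stated. Of participants in general, the section says: "They will receive interventions and undergo assessments at scheduled visits". Section 2.7 refers to a table for the detail: "The schedule for enrollment, interventions, assessment, and visits of the participants are shown in Table 1". That table is not reproduced in the text at hand.

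Section 2.10 describes the trial as open-label for patients and practitioners. Section 2.13 plans a safety test on the intent-to-treat and per-protocol sets, and does not define it further. Under section 2.12, site principal investigators judge whether events are related to acupuncture and whether the trial should be amended or ended.

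**The concern.** A rule that asks about events at every visit is even-handed only if the arms have similar numbers of visits. Here the treatment itself generates visits. Section 2.4 places interventions and assessments together at scheduled visits, so a needling session is naturally read as a visit at which events are asked about.

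Someone asked every few days will mention a cold, a headache or period pain that someone asked once a month may have forgotten. With equal true rates, more such events would then be recorded under acupuncture. The distortion runs against acupuncture, and it concerns general events: a reaction to needling cannot occur in a control.

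The pilot is meant to inform a full-scale trial of efficacy and safety, so an uneven safety signal could be carried forward. The analysis cannot repair this later, because an event that was never elicited from a control is not in the data.

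**Working it through.** **Contact counts, from section 2.4**

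- Acupuncture: 10 sessions per 4 weeks × (16 / 4) = 40 sessions, which reproduces the stated total. The mean interval is 112 days / 40 = 2.8 days.
- Control: monthly for 16 weeks gives about 4 contacts, or 5 if both ends are counted. The interval is about 28 days.
- Ratio: 40 / 4 = 10, or 40 / 5 = 8.

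This applies to the 16-week treatment period. The article describes no arm-specific contacts in the 16-week follow-up.

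**What the imbalance could do to counts**

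The documents give no recall or self-recording rates, so the following inputs are assumptions shown over a range:

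- the true rate of transient events is the same in both arms;
- the chance of reporting an event when asked decays exponentially with the time since it occurred, with half-life h of 3, 7, 14 or 28 days;
- every acupuncture session and every monthly control contact includes an enquiry;
- self-recording captures a fraction d of events, independently of the enquiry and equally in both arms.

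With λ = ln 2 / h and interval T between enquiries, the mean fraction captured by enquiry is f(T) = (1 − e^(−λT)) / (λT). Adding self-recording gives F = 1 − (1 − f)(1 − d). The spurious ratio is F at T = 2.8 divided by F at T = 28.

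Example, h = 7 and d = 0:

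- T = 2.8: λT = 0.277, f = 0.873.
- T = 28: λT = 2.773, f = 0.338.
- Ratio: 0.873 / 0.338 = 2.58.

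The same case with d = 0.5:

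- Acupuncture: 1 − 0.127 × 0.5 = 0.937.
- Control: 1 − 0.662 × 0.5 = 0.669.
- Ratio: 0.937 / 0.669 = 1.40.

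| Half-life (days) | f, acupuncture | f, control | Ratio, d = 0 | Ratio, d = 0.5 | Ratio, d = 0.8 | Ratio, d = 1 |
|---|---|---|---|---|---|---|
| 3 | 0.736 | 0.154 | 4.77 | 1.50 | 1.14 | 1.0 |
| 7 | 0.873 | 0.338 | 2.58 | 1.40 | 1.12 | 1.0 |
| 14 | 0.934 | 0.541 | 1.73 | 1.25 | 1.09 | 1.0 |
| 28 | 0.966 | 0.721 | 1.34 | 1.14 | 1.05 | 1.0 |

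The d = 0 column is an upper value, because the protocol does ask participants to record events. The imbalance disappears only when self-recording is complete.

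**The case against.** The strongest objection is that the 8- to 10-fold figure depends on what counts as a visit, and the schedule sits in a table that cannot be seen. The article also uses the word in a numbered sense (the random number is given at the second visit), and adherence is checked every 4 weeks. A 4-weekly assessment schedule common to both arms cannot be excluded. This stands, and it makes the point conditional. It does not remove it, because the visible rule covers every visit without restriction. Even with common assessment visits, staff could learn of events at 40 sessions, and the article states no separation of events by source.

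Second, self-recording is independent of visits and of arm. This stands in part: it shrinks the ratio considerably, but removes it only if complete.

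Third, laboratory safety is scheduled alike in both arms, and investigators judge relatedness. The first point is true but covers no symptomatic events. The second helps only in part, since those investigators are not said to be blinded.

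Fourth, scripted questions and source flags normally belong in the full protocol, the CRF or the SAP. Their absence from an article is indeed no finding. The point rests on the enquiry rule that the article does state.

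A reader might go further and infer that the safety comparison is biased, that counts from all sources are pooled, or that safety is an objective of this pilot. The documents do not support these readings. They neither define a between-arm comparison of event counts nor describe pooling, and the introduction names efficacy and safety as what the full-scale trial would evaluate; the pilot's own objective is feasibility.

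**Conclusion.** The point holds as a conditional risk. As written, and unless Table 1 confines enquiry to visits common to both arms, the rule has staff asking about events some 8 to 10 times as often under acupuncture during the 16 treatment weeks. Any between-arm comparison of mild or transient events would then tend to make acupuncture look less safe.

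The size depends on assumed recall half-lives of 3 to 28 days and on how completely participants self-record: from 4.8 down to 1.3 with no self-recording, about 1.5 to 1.1 at 50% capture, about 1.14 to 1.05 at 80%, and none at 100%. With reasonably good self-recording the distortion is modest. The case for acting is that the correction is cheap and cannot be made after the data are collected.

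**What to change.** In section 2.6, state that any between-arm comparison of adverse events uses the same structured enquiry in both arms at common time points, every 4 weeks to week 16 and then at week 32, together with participants' self-records. Flag in the CRF whether each event came from the common enquiry, from self-recording or from an acupuncture session. Report events noted only at sessions separately and descriptively, for the acupuncture arm. If Table 1 already limits enquiry to common visits, say so in the text; the source flag and separate reporting are still worth adding.

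The cost is a short addition to the safety section, one CRF field, and one standard question to controls at contacts that already take place about monthly. Events noted at sessions are still recorded and reported.

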### Participant timeline

2.7

The schedule for enrollment, interventions, assessment, and visits of the participants are shown in Table 1.

### Sample size

2.8

We calculated the sample size based on a previous study that used the same variables as ours as the primary outcome.^[12]^ For the current study, the mean difference and standard deviation are assumed as 0.14 and 0.17, respectively, between the acupuncture and control groups. In other words, the effect size for menstrual frequency is assumed to be approximately 0.8. In our study, participants will be randomized into 2 groups in a 1:1 ratio after considering 5% of the significance level (α) and 80% of the power (1−β). Therefore, the present study will include 50 participants in total, divided into 2 groups of 25. Considering a dropout rate of 15%, at least 60 participants are required.

### Randomization and allocation concealment

2.9

In this trial, participants will be randomly assigned to either the acupuncture group or control group in a 1:1 ratio using a table of random numbers. An independent, blinded statistician will generate random numbers using the block randomization method of SAS version 9.4 (SAS Institute. Inc., Cary, NC) with a block size of 4. The investigator will be subsequently notified of the number assigned to each participant, and the participants will be given a random number on their second visit. The allocation table of participants will be kept by an independent statistician until the end of the study. The clinical research coordinator (CRC) will enroll the participants, generate the allocation sequence, and assign participants to the intervention groups.

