### Blinding

2.10

This is an open-label trial; therefore, neither the patients nor the practitioners will be blinded to the entire process. However, other researchers, including outcome assessors and statisticians, will be blinded to eliminate potential bias. Assessors, who are not involved in randomization or acupuncture performance, will ask simple and necessary questions to participnats for outcome assessments so that they cannot assume the groups of each participant.

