### Data collection methods and management

2.11

All research assistants, including the CRCs at the 3 centers, will be trained using a standard operating procedure to promote data quality. The laboratory data will be analyzed in the medical laboratories of South Korea and China that meet the international standard ISO 15189^[^28^,^^29^^]^ to reduce errors between each center.

Data collection procedures will be conducted in compliance with the approved protocol and the standard operating procedure of the trial to ensure good data quality. All data, including the CRF and worksheet, will be kept in a cabinet with locking devices. At the end of the trial, all data written in the CRF will be coded in separate computer files. Data entry will be performed using a double-input method, and the matching work will be conducted after reviewing inconsistent data. When the data are matched, a data clarification form will be completed and validated, and the resolution will be reflected in the data. Computer files in computer storage devices will be kept confidential under password protection during and after the trial.

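### Section 2.9 gives generation of the allocation sequence both to an independent statistician and to the coordinator who enrols and assigns, which puts concealment at risk

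*Protocol article*

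**What the plan says.** Three statements in section 2.9 (Randomization and allocation concealment) bear on who makes and holds the list.

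- Generation, first statement: "An independent, blinded statistician will generate random numbers using the block randomization method of SAS version 9.4", "with a block size of 4".
- Custody: "The allocation table of participants will be kept by an independent statistician until the end of the study". The investigator is told each participant's number afterwards, and participants receive it at their second visit.
- Generation, second statement: "The clinical research coordinator (CRC) will enroll the participants, generate the allocation sequence, and assign participants to the intervention groups".

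Three points elsewhere set the context.

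- Section 2.10 (Blinding): "This is an open-label trial; therefore, neither the patients nor the practitioners will be blinded to the entire process". Outcome assessors and statisticians are to be blinded.
- Section 2.11 places the coordinators at the hospitals: "All research assistants, including the CRCs at the 3 centers, will be trained using a standard operating procedure".
- Section 2.13 analyses the primary outcome by analysis of covariance, with baseline menstrual frequency as covariate and treatment group as fixed factor.

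**The concern.** Allocation concealment requires that whoever decides on enrolment cannot know the next assignment. The last sentence of section 2.9 puts enrolment, sequence generation and assignment in one pair of hands at the site. The sentences before it keep generation and custody away from the site. Staff following the text cannot tell which rule applies, and one of the two defeats the purpose named in the section heading.

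Foreknowledge lets a recruiter steer who is enrolled when a given arm is next. The article leaves room for this: exclusion criterion 12 in section 2.3.2 is open to investigator judgement. Section 2.4 drops participants whose adherence to acupuncture falls below 70%, so expected adherence is a natural thing for a recruiter to weigh. Features of that kind are not in the covariance model. Assessor blinding begins after allocation and does not act on how the groups were formed. With about 30 women per arm, a few steered enrolments could matter to the primary comparison.

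**Working it through.** **1. The two rules side by side**

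| Task | Earlier sentences of 2.9 | Last sentence of 2.9 |
|---|---|---|
| Generate the sequence | independent, blinded statistician | coordinator |
| Keep the table | independent statistician, to study end | not stated |
| Enrol | not stated | coordinator |
| Assign to groups | investigator is notified of the number | coordinator |

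The first row is a direct conflict. The coordinators are centre staff (2.11), so they cannot be read as the independent statistician under another title. A person who generates the list also knows it, so custody by someone else no longer conceals it from that person.

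**2. Size if the coordinator sentence governs**

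All 60 allocations can be known before enrolment.

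**3. Size if the statistician rule governs**

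Inputs: ratio 1:1 and block size 4 (2.9), 60 participants (2.8), three hospitals (2.1), arms visible once treatment starts (2.10). The assumptions are that site staff know the block size and that blocks are complete (60/4 = 15 blocks). The article does not say whether there is one list or one per hospital, so both ends of the range are shown.

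*Upper end: the recruiter sees every earlier assignment on the list* (a separate list per hospital, or all assignments visible). There are 6 possible blocks.

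- Places 1 and 2 are never determined.
- Place 3 is determined when the first two are alike: probability 1/3.
- Place 4 is always determined: probability 1.
- Share determined: (0 + 0 + 1/3 + 1)/4 = 1.333/4 = 33%. Over 15 blocks: 15 × 1.333 = 20 of 60.
- Best guess correct: (1/2 + 2/3 + 2/3 + 1)/4 = 2.833/4 = 71%, against 50% by chance.

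*Lower end: one central list, three equally recruiting hospitals in random order, only own-hospital assignments visible, position in the block known.* Each earlier participant is at the recruiter's hospital with probability 1/3.

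- Place 3: the first two are alike (1/3) and both at the own hospital (1/9), giving 1/27.
- Place 4: three earlier assignments split two to one. The last is certain if both majority-arm assignments were at the own hospital, giving 1/9 = 3/27.
- Share determined: (1/27 + 3/27)/4 = 1/27 = 3.7%. Over 60 participants: 60/27 = 2.2, about 2.

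**4. Cost of varying the block size**

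The largest imbalance within one list arises when recruitment stops mid-block after all of one arm has been drawn. That is 2 for blocks of 4 and 3 when blocks of 6 are also used.

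**The case against.** The strongest reply is that the last sentence is a drafting slip. Two sentences place generation and custody with a statistician, the investigator learns numbers only afterwards, and the number is given at the second visit. Read as a whole, the section points towards a concealed list. This stands as a limit. A reader might infer that concealment has been removed, but the article does not show that; it shows that concealment fails if one of two conflicting sentences is followed. The reply does not dissolve the conflict, because both sentences are stated outright and no reading satisfies both. A fuller protocol could show which was meant but would not make this text consistent.

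A reader might also take 20 foreseeable allocations of 60 as a plain consequence of the block size. That figure needs the recruiter to know the block size and to see every earlier assignment on the list. The article reports the block size but does not show that site staff would know it during enrolment. With one central list the figure can be about 2. A fixed block of 4 contradicts nothing in the article.

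Selection of women with milder oligomenorrhea would be a poor example of bias that analysis cannot repair. Baseline menstrual frequency is the covariate, so an imbalance there is at least largely adjusted. The argument rests on unmeasured features.

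Finally, the lack of sealed envelopes or a central release step is not a fault in itself. A journal article may leave such mechanics to the full protocol.

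**Conclusion.** The point holds as an internal contradiction on who generates the allocation sequence, and it must be resolved. Its consequence is conditional: full foreknowledge (60 of 60) if the coordinator sentence is carried out, and a list that can be concealed if the statistician sentences are. Because patients and practitioners are unblinded, and neither covariance adjustment nor blinded assessment repairs selection on unmeasured features, the text should not leave this open.

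The fixed block size is secondary and is an improvement to make rather than an error. Its effect runs from about 4% to 33% of allocations determined in advance, under the assumptions stated in the calculation. The article does not let a reader choose between the ends, and nothing in it shows that allocations will in fact be foreseen.

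**What to change.** Required: in the last sentence of section 2.9, delete the clause that has the coordinator generate the sequence. State that the independent statistician alone generates and holds the list, and that the coordinator only enrols and receives each participant's assignment after enrolment. This is a wording amendment; no sample size or analysis changes.

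Recommended: replace the single block size of 4 with randomly varying sizes, for example 4 and 6, not disclosed to site staff, and say whether the list is central or separate for each hospital. This takes a few lines of SAS. The price is a maximum end-of-list imbalance of 3 instead of 2.
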